### Outcomes {12}

#### Primary outcome

Time to clinical improvement (TTCI)—the TTCI was defined as proposed by the Cap-China Network [18] and thereafter utilized in the LOTUS China trial [3] and recommended by the World Health Organization (WHO) [19]. Briefly, TTCI refers to the time from randomization to an improvement of two points on the seven-category ordinal scale stated below [3] or live discharge from the hospital:
Not hospitalized with the resumption of normal activitiesNot hospitalized, but unable to resume normal activitiesHospitalized, not requiring supplemental oxygenHospitalized, requiring supplemental oxygenHospitalized, requiring nasal high-flow oxygen therapy and non-invasive mechanical ventilationHospitalized, requiring ECMO, invasive mechanical ventilation, or bothDeath

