### Sample size {14}

We used information from the previously published LOTUS [3] trial evaluating the effect of lopinavir-ritonavir on time to clinical improvement (TTCI) [censored at day 28], since there is no information on the effect of icatibant or C1 esterase inhibitor for this primary outcome. This approach resulted in a hazard ratio of 1.24 for clinical improvement. It is also relevant to take into account the emergency situation and the high costs involved. The sample size was determined based on the formula for the proportional hazard regression model (Schoenfeld, 1983). We assumed a 5% type 1 error (alpha), power test of 80%, drop-out (censure) rate of 20%, and hazard ratio between treatment and the standard care alone varying from 1.2 to 2.0. To extend the calculations for a three-arm trial, we considered the three groups of the same size and the comparison of the two treatments separately to standard care alone, but without comparing the two treatments to each other. In other words, the same standard care alone group will be compared with each treatment group. Additionally, we set alpha at 2.5% to allow for multiple testing and multiplied the sample size by 1.5. Figure 2 presents the total sample size required for this setup and according to different hazard ratios. Assuming a hazard ratio of 1.9, we obtained a final sample size of 174 (58 per group).

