## Assignment of interventions: allocation

### Sequence generation {16a}

We will use a software-based approach (www.sealedenvelope.com) to generate the allocation sequence using a blocked randomization with randomly selected block sizes, with 3, 6, or 9 subjects per block. To reduce the probability of imbalance between the groups with regard to severity, we have set up a stratification approach using two strata: (1) no oxygen support needed or oxygen support < 3 L/min delivered by nasal catheter; (2) high-flow oxygen support delivered by nasal catheter between 3 L and 6 L/min or up to 10 L/min by non-rebreather face mask, 35% oxygen through a Venturi mask, non-invasive ventilation, or mechanical ventilation or eventually ECMO.

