## Statistical methods

### Statistical methods for primary and secondary outcomes {20a}

All our statistical analyses will follow the intention-to-treat principle. For the primary outcome, we will use the Kaplan-Meier estimator and log-rank test to respectively estimate and compare the survival curves, followed by a Cox proportional hazards model to adjust for baseline explanatory variables in the final data analysis. Multiple imputation will be used to impute missing data. The following covariates will be settled: age, sex, duration of symptoms before enrollment, use of oxygen support prior to enrollment, and presence of relevant comorbidities. This analysis will be performed to compare each treatment arm, that is, the icatibant plus standard care group and the C1 esterase group inhibitor plus standard care, with the standard care group alone. In the analysis of secondary endpoints involving time to event, such as duration of mechanical ventilation (days) and length of hospitalization in survivors (days), we will also use the Cox proportional hazards model. The logistic regression model will be used to analyze secondary binary endpoints.

The statistical analysis plan (SAP) containing all the details of the analysis will be finalized and made available to the DSMC before the final analysis.

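### The starting category on the seven-point scale decides which primary event a patient awaits, yet the log-rank test is not stated to be stratified on it and the Cox model carries it only if the oxygen covariate is coded by level of support; power may be forgone.

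*Protocol article*

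**What the plan says.** The protocol (Primary outcome) measures time from randomisation to "an improvement of two points on the seven-category ordinal scale stated below", or to live discharge. Everyone enters as an inpatient, so baseline categories run from 3 to 6, and these differ only in level of respiratory support.

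For the comparison, section {20a} names Kaplan-Meier curves and a log-rank test, with no stratification stated, "followed by a Cox proportional hazards model to adjust for baseline explanatory variables in the final data analysis". The covariate list is: "The following covariates will be settled: age, sex, duration of symptoms before enrollment, use of oxygen support prior to enrollment, and presence of relevant comorbidities". Neither the scale category at randomisation nor the randomisation stratum is named. The coding of the oxygen term is not given, and details are deferred to the SAP. The interim section {21b} uses a Cox model without naming covariates.

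Sequence generation {16a} has two strata. The first begins "no oxygen support needed or oxygen support" and stops below 3 L/min by nasal catheter. The second starts at 3 L/min and runs through face masks to "35% oxygen through a Venturi mask, non-invasive ventilation, or mechanical ventilation or eventually ECMO".

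**The concern.** Set the outcome definition against the starting categories:

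| Start | Two points better | Event in practice |
|---|---|---|
| 3 | 1 | live discharge |
| 4 | 2 | live discharge |
| 5 | 3 | in hospital, off oxygen |
| 6 | 4 | in hospital, on supplemental oxygen |

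Patients in different categories await different events, which probably occur at different rates. If a strong baseline predictor is left out of a time-to-event comparison, the estimated hazard ratio moves toward 1 and power falls. A yes/no oxygen term would put categories 4, 5 and 6 in one group. Given the hypoxaemia entry criteria, few patients are likely to be off oxygen, so such a term would separate little.

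The randomisation strata do not map onto the categories. Stratum 1 holds category 3 and the low-flow part of category 4. Stratum 2 holds the rest of category 4 with categories 5 and 6. The stratum text attaches the term high-flow to 3 to 6 L/min by catheter, but even if those patients were scored as category 5, mask oxygen, non-invasive ventilation and invasive ventilation would still share a stratum. With 58 per arm, a chance imbalance in ventilated patients within stratum 2 would also go uncorrected; that risk is not quantified here.

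**Working it through.** **1. The plan's own figure.** Inputs from Sample size {14}: hazard ratio 1.9, power 80%, 20% censoring, and "we set alpha at 2.5% to allow for multiple testing and multiplied the sample size by 1.5". Sidedness is not stated; two-sided reproduces the result.

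- Events per comparison (Schoenfeld) = 4(z₀.₉₈₇₅ + z₀.₈₀)² / (ln 1.9)² = 4(2.241 + 0.842)² / 0.412 = 92.3, rounded up to 93.
- Total = 92.3 / 0.8 × 1.5 = 173.0, that is 58 per group, or 174 as stated.
- One comparison has 116 patients and 116 × 0.8 = 92.8 events, giving power of 80.2%.

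The formula has no covariate term, so adjusting for the category does not change the planned number.

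**2. Simulated power, stratified comparison.** The protocol gives neither the baseline mix nor event rates by category, so both are assumed. Design: 58 v 58, true hazard ratio 1.9 within category, two-sided 2.5%, about 80% events, exponential times, daily assessment, censoring at day 28, allocation balanced within the two strata. Log-rank tests, 2,500 trials per scenario. Assumed mix: category 3 10%; category 4 below 3 L/min 30%; category 4 at 3 L/min or more 25%; category 5 20%; category 6 15%. The gradient is the assumed 28-day control improvement in those five groups. A second simulation on the same mix (run B) used category alone as the finest adjustment; run A used stratum plus category.

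| Gradient | Run | Unadjusted | Oxygen yes/no | Stratum | With category |
|---|---|---|---|---|---|
| Weak (80/80/75/65/50%) | A | 76 | 76 | 78 | 78 |
| | B | 77 | 75 | 78 | 77 |
| Moderate (88/88/80/60/40%) | A | 67 | 68 | 74 | 78 |
| | B | 70 | 70 | 76 | 79 |
| Steep (92/92/85/55/30%) | A | 56 | 58 | 70 | 76 |
| | B | 54 | 57 | 69 | 77 |

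Gain from category over oxygen yes/no: weak 78 − 76 = 2 and 77 − 75 = 2; moderate 78 − 68 = 10 and 79 − 70 = 9; steep 76 − 58 = 18 and 77 − 57 = 20. Gain over the stratum: weak 0 and −1; moderate 4 and 3; steep 6 and 8. The same cell differs by up to 3 points between runs, so gains of 1 to 3 points should not be read closely. With no gradient, stratifying on category cost about 3 points in run A and about 2 in run B.

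**3. Sensitivity, Cox model with category as a covariate.** Conditional hazard ratio 1.9, 116 patients, 20% censored, 1,500 runs per scenario. Assumed improvement hazard ratios against category 4, for categories 3/5/6: mild 1.25/0.75/0.5; moderate 1.5/0.5/0.25; strong 2/0.35/0.12. Power (%) is shown as oxygen yes/no / stratum / category.

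| Mix of 3/4/5/6 | Mild | Moderate | Strong |
|---|---|---|---|
| 10/70/15/5% | 77/77/78 | 75/76/81 | 67/69/80 |
| 10/50/20/20% | 74/75/77 | 63/68/79 | 48/58/79 |
| 15/40/25/20% | 77/77/80 | 65/69/78 | 49/57/78 |

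The direction is the same, and the losses are larger where more patients are ventilated and category effects are extreme. The mechanism shows in the second mix with a moderate effect: the average estimated hazard ratio was 1.70 unadjusted, 1.74 with oxygen yes/no, 1.79 with stratum and 1.94 with category. With no category effect, category and oxygen yes/no gave the same power to within half a point.

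**The case against.** The strongest reply is that the category is not really absent. Categories 3 to 6 are levels of respiratory support, and the listed oxygen covariate, coded by level, would carry the category in full. How a named covariate is coded commonly sits in the SAP, which is not shown. This stands: a reader might infer that the model discards the baseline category, but the protocol supports only that the category is not named. What remains is that the wording fits a yes/no reading equally well, refers to the time before enrolment while the outcome clock starts at randomisation, and does nothing for the log-rank test, which is the first-named comparison.

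It is also fair that nothing here is invalid. An unstratified log-rank test in a randomised trial keeps its type I error. A reader might further infer that true power is below the stated 80%. The protocol does not support that: the calculation reproduces, and if 1.9 is taken as the marginal hazard ratio, the 80% is untouched and adjustment is a gain on top of it.

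The mix and rates are assumed, and the simulations leave out age, sex, symptom duration and comorbidities, which may carry some of the same information. Severity is partly handled elsewhere too, through stratified allocation and a planned severity subgroup analysis. These points limit the size of the claim. They do not make the two strata equivalent to the four categories.

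**Conclusion.** The point holds as one of efficiency and clarity, not of validity. The starting category sets the event. No stratification of the log-rank test is stated, the Cox list captures the category only under one coding of the oxygen term, and the randomisation strata recover only part of it. On the section 2 assumptions, the power forgone against oxygen yes/no is about 0 to 2 points (weak gradient), about 10 (moderate) or about 20 (steep), and against the stratum alone about 0 to 8 points. The harsher assumptions of section 3 give more: up to 31 points against oxygen yes/no (79 − 48) and 21 against the stratum (79 − 58, 78 − 57). The protocol cannot say where in this range the trial lies; if the category does not predict improvement, nothing is lost. The change is worth making because it is cheap, not because a shortfall has been shown.

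**What to change.** In section {20a}:

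- Define the oxygen covariate as the seven-category score at randomisation (3, 4, 5, 6).
- Stratify the primary log-rank test and the Cox model on that score, with a rule set in advance for collapsing near-empty categories.
- Keep the randomisation stratum as a term in the Cox model. If catheter oxygen is scored as category 4, the stratum then serves only to split category 4 at 3 L/min.

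In the interim section {21b}, state that the same Cox model is used.

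The cost is a sentence or two. The score must already be recorded to determine the primary event, so no new data are needed. The downside is about 2 to 3 points of power if the category proves unrelated to outcome.

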Another important function of the ACE system is the inactivation of the potent inflammatory substance bradykinin [8]. Accumulation of bradykinin in the lungs is a common side effect of ACE inhibitors leading to cough [9]. In animal models, the inactivation of ACE2 leads to severe acute pneumonitis in response to lipopolysaccharide (LPS), and the inhibition of bradykinin almost completely restores the lung structure [10].

In COVID-19 patients, rapidly progressing pneumonia is the main clinical feature associated with severe outcomes [2]. This is accompanied by high levels of C-reactive protein, indicating the magnitude of the inflammatory response [2]. Thus, we hypothesized that increased bradykinin, and not AII, is the main link between SARS-CoV-2 inhibition of ACE2 and severity of the disease. The abnormalities of the ACE system in hypertensive and diabetic patients, potentially associated with the chronic use of ACE inhibitors, could predispose to a massive increase in lung bradykinin leading to rapidly progressing pneumonia.

Currently, inhibition of bradykinin is the main therapeutic approach to treat a rare disease known as hereditary angioedema [11]. There are three major pharmacological approaches used to dampen bradykinin activity: (i) inhibition of bradykinin synthesis using either the human-derived inhibitor of C1e/kallikrein [12] or (ii) a synthetic inhibitor of kallikrein [13] and (iii) inhibition of bradykinin receptor 2 [14]. We propose the ITHACA trial (COVID-19 Treated by c1 esterase inHibitor And iCAtibant) to assess the efficacy and safety of the inhibitor of C1e/kallikrein and the inhibitor of bradykinin receptor 2 compared to standard care alone in the treatment of patients with pneumonia caused by COVID-19. We have designed a three-arm study to increase efficiency and reduce costs, since the same control arm will be used for comparison with two different drugs. In addition, this design increases the likelihood that the participant will be allocated to a treatment arm, which usually increases the chance of enrollment.

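### Adding baseline CRP and SOFA to the adjusted Cox model would cost almost nothing and could gain power; leaving them out is an inefficiency, not an error

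*Protocol article*

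**What the plan says.** - **Primary analysis** (Statistical methods {20a}): "we will use the Kaplan-Meier estimator and log-rank test to respectively estimate and compare the survival curves". The covariate-adjusted Cox model comes after this, as a second step. The adjustment covariates are "age, sex, duration of symptoms before enrollment, use of oxygen support prior to enrollment, and presence of relevant comorbidities". Each active arm is compared with standard care in this way, and multiple imputation is planned for missing data.
- **Baseline measurements** (Participant timeline {13}, Table 1): SOFA and CRP are both marked in the allocation column. They stand below a laboratory-tests row whose note limits testing to every fourth day or the physician's discretion.
- **Rationale** (Background {6a}): rapidly progressing pneumonia is named as the main feature of severe outcomes and is said to come with "high levels of C-reactive protein, indicating the magnitude of the inflammatory response". That inflammation is what the two drugs are meant to reduce. SOFA is not mentioned there.
- **Randomisation** (Sequence generation {16a}): there are two strata, defined by level of oxygen support.
- **Sample size** ({14}): "The sample size was determined based on the formula for the proportional hazard regression model (Schoenfeld, 1983"), and "we set alpha at 2.5% to allow for multiple testing and multiplied the sample size by 1.5". With 80% power, 20% censoring and a hazard ratio of 1.9, the result is 174 patients, 58 per group. No covariate enters.

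**The concern.** None of the five listed covariates measures inflammation or organ dysfunction. Oxygen support stands in for severity, but the list does not say how finely it is graded. The upper randomisation stratum runs from 3 L/min by nasal catheter to mechanical ventilation or ECMO, so patients who share a category may differ a good deal in CRP and SOFA.

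In a Cox model, leaving out a variable that predicts the outcome lowers the power of the treatment test and moves the estimated hazard ratio towards 1, even when the arms are perfectly balanced on it. The protocol already schedules both values at allocation, so any such loss could be avoided without new data. What is at stake is the precision of the adjusted comparison, not its validity.

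**Working it through.** **1. The plan's own figure.** Inputs from Sample size {14}: hazard ratio 1.9, alpha 2.5% per comparison (two-sided is not stated, but it is the version that reproduces the total), power 80%, 20% censoring, equal arms, multiplier 1.5.

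- Events = 4 × (2.241 + 0.842)² / (ln 1.9)² = 92.3
- Patients in two arms = 92.3 / 0.80 = 115.4, rounded up to 116 (58 per arm)
- Three arms = 116 × 1.5 = 174, as stated
- Expected events per comparison = 116 × 0.80 = 92.8, which gives power of 80.2%

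The figure reproduces exactly with no covariate term, so adding or omitting CRP and SOFA does not change it.

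**2. The log-rank test.** It uses no covariates. The list cannot change its power.

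**3. The adjusted Cox model.** The documents give no prognostic strength for CRP or SOFA, so it was assumed over a range. The SD below is their joint effect on the log-hazard scale beyond the listed covariates. Both simulations have 58 per arm, about 80% events, two-sided 2.5% and a hazard ratio of 1.9 conditional on all covariates.

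- Simulation A: listed covariates SD 0.6, two extra covariates, 12,000 replicates per setting.
- Simulation B: listed covariates SD 0.5, one extra score, 1,500 replicates (1,000 at SD 0.6). In its SD 0 row the listed covariates also have no effect.

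| Residual SD (assumed) | Simulation | Power without | Power with | Change, points |
|---|---|---|---|---|
| 0 | A | 79.1% | 78.5% | −0.6 |
| 0 | B | 81.5% | 81.4% | −0.1 |
| 0.2 | A | 76.9% | 78.7% | +1.8 |
| 0.2 | B | 77.7% | 80.2% | +2.5 |
| 0.3 | A | 74.8% | 78.7% | +3.9 |
| 0.4 | B | 70.8% | 77.8% | +7.0 |
| 0.5 | A | 66.7% | 78.2% | +11.5 |
| 0.6 | B | 65.0% | 79.4% | +14.4 |

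In B the average hazard ratio without and with the extra score was 1.90 and 1.93 (SD 0.2), 1.81 and 1.92 (SD 0.4), and 1.74 and 1.94 (SD 0.6).

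**4. If 1.9 is the effect seen without CRP and SOFA.** Simulation A then gives power without and with them of 79.5% and 81.1% (SD 0.2), 80.6% and 84.1% (SD 0.3), and 80.4% and 89.6% (SD 0.5). Planned power is intact, and adding them gains 1.6, 3.5 and 9.2 points.

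**5. No true effect.** Simulation A rejected in 2.9% with and without the extra covariates. Simulation B (SD 0.4, 1,000 replicates) rejected in 3.0% without and 3.7% with them, at an average hazard ratio of 1.01 in both. The Monte Carlo standard error of a 2.5% rate at 1,000 replicates is √(0.025 × 0.975 / 1,000) = 0.5 point, and the larger simulation shows no difference. Omitting the covariates creates no bias and no excess of false positives.

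**6. Room in the model.** Treatment, five listed covariates at one parameter each, and two more make 8 parameters: 92.8 / 8 = 11.6 events per parameter at the end. With half the events at the interim it is 46.4 / 8 = 5.8.

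**The case against.** A reader might infer that the primary comparisons are underpowered and their hazard ratios biased. The documents do not support either inference.

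- **Power.** The log-rank test is unaffected, and the planned 80% is intact if 1.9 is the effect without CRP and SOFA. The lower figures in step 3 arise only if 1.9 is taken as conditional on them, which Sample size {14} does not say.
- **Bias.** The smaller hazard ratio reflects non-collapsibility: the shorter model targets a less conditional effect. It is not a distorted estimate of the same one.

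Further points count against a large gain:

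- The strength of CRP and SOFA is unknown, and the rationale gives no effect size for CRP.
- SOFA has a respiratory component and so overlaps with oxygen support. The background reports shock in only 13% and kidney failure in 6% of severe cases, and the exclusions remove severe renal and liver disease. Both narrow what SOFA could add.
- The laboratory-test note in Table 1 means that complete baseline values are not assured.
- A short pre-specified list that includes the severity marker used for stratification is defensible, and no passage promises more.

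All of this stands. It lowers the expected gain and rules out calling the list an error. It does not show harm from adding the two variables: the cost in the worst case simulated is 0.6 point, and imputation is already planned.

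**Conclusion.** The point holds as an efficiency improvement to the adjusted Cox comparison and no further. Nothing in the protocol is wrong or contradictory here.

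The gain is about 2 to 14 points of Cox power if CRP and SOFA together carry a residual SD of 0.2 to 0.6 on the log-hazard scale, and 1.6 to 9.2 points for SDs of 0.2 to 0.5 if 1.9 is read as the effect without them. If they predict nothing, the cost is under 1 point. The strengths are assumptions, as are proportional hazards and covariates independent of one another; the documents do not show which setting applies. Given the overlap of SOFA with oxygen support, the lower part of the range is the safer expectation.

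**What to change.** In Statistical methods {20a}, add baseline CRP (log-transformed) and baseline SOFA to the pre-specified covariates of the final adjusted Cox model, for both comparisons with standard care. Enter both as continuous, using the allocation value in Table 1, and handle missing baseline values by the multiple imputation already planned. Make the change before any analysis by arm, so that the choice cannot depend on results.

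The Interim analyses section names a Cox model without covariates. With about half the events there, the SAP should decide whether the longer list is used.

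Cost: one sentence and two more parameters on about 93 events per comparison, with no new patients or visits. If it is made in the protocol, the protocol's own rule on amendments sends a change to the statistical analysis to the ethics committee. If the sponsor prefers the short list, a line giving the reason would be enough.

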### Interim analyses {21b}

We will perform an interim analysis for effectiveness, futility, and safety when we have reached 50% of the events between all groups (three arms).

The Cox proportional hazards model will be used to evaluate the primary outcome in this interim analysis. The logistic regression model will be used to evaluate the occurrence of severe adverse events as a secondary endpoint.

An independent statistician will perform the interim analyses, and the results will be evaluated by the DSMC.

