## Methods: participants, interventions, and outcomes

### Study setting {9}

This is a single-site study, and all procedures will be conducted at the Clinical Hospital at the University of Campinas in wards and intensive care units specifically focused on the care of patients with COVID-19. The expected enrollment start date is April 21, 2020, and the expected end date is July 21, 2020.

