### Methods of analysis to handle protocol non-adherence and any statistical methods to handle missing data {21c}

We will use multiple imputation for missing data. A per-protocol analysis will be used to check the robustness of the results obtained primarily by the intention-to-treat principle.

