### Adverse event reporting and harms {22}

The project investigators will prepare reports according to the adverse event data collected by themselves.

Both adverse events (AEs) and serious adverse events (SAEs) will be collected throughout the follow-up period, from the time of informed consent to day 28 of evaluation. The serious adverse events that occur after day 28 will be evaluated by the investigators and the DSMC to determine whether they have any relation with the experimental drug under study.

All SAEs will be accompanied by study physicians until there is total or at least significant improvement.

Following the International Conference on Harmonization Guidelines for Good Clinical Practice, all AEs will be investigated in detail and included in an electronic CRF (REDcap). The information collected will include the following: start date of possible AE, reported signs and symptoms, relationship between the reported event and the drugs studied, outcome of the adverse event, and the dates on which the data were evaluated by the DSMC.

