We chose to define our study population as patients hospitalized due to COVID-19 pneumonia precisely because we considered that patients with severe disease would be those who would benefit most from reduced hyperinflammatory status. The choice of outcome as the time to event (improvement of the ordinal scale of seven items or hospital discharge) was based on previous clinical studies (LOTUS and Remdesivir trial). We consider that this outcome will allow us to evaluate whether in fact the drugs tested contribute to a reduction of morbidity over time. In addition, it will help us to infer whether the use of intervention could mean a shorter stay. As the outcome is the same as in previous studies, we will also have the benefit of literature comparison.

We will be using a multi-arm design to increase study effectiveness and reduce costs. C1 esterase and icatibant were selected because they are the only two drugs that inhibit the bradykinin pathway that have been approved for use in patients in Brazil. In addition, they require short-term use (only 4 days) and already have a safe and effective dose established for use in hereditary angioedema.

We chose standard care as the comparator only because we believe that there are no clinical trials with sufficient impact to indicate any specific treatment for COVID-19 pneumonia. Therefore, the use of any specific drug in our study would be unethical. The use of a placebo is not possible, since the development of two placebos identical to the interventions, one of intravenous infusion and another of subcutaneous infusion, would require a lot of time and would significantly increase costs. Blinding is also not possible in this study. We cannot blind the assisting physician either because of safety issues or because she/he will be responsible for prescribing the experimental drug. In addition, the absence of a placebo would make it much easier for the patient to guess that she/he was selected for the intervention. This is the first attempt at evaluating the use of bradykinin pathway inhibitors in pneumonia caused by COVID-19. We believe that the results will be of great importance for hospital management of the disease at the global level.

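### The interim logistic model for severe adverse events cannot use the partial follow-up of patients still inside the 28-day window; a censored time-to-first-event analysis can, at almost no cost

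*Protocol article*

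**What the plan says.** In the Protocol article, section Interim analyses {21b}, one look serves three purposes: "We will perform an interim analysis for effectiveness, futility, and safety". It takes place "when we have reached 50% of the events between all groups (three arms"). No minimum follow-up per patient is stated.

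The same section names two models. For efficacy: "The Cox proportional hazards model will be used to evaluate the primary outcome in this interim analysis". For harm: "The logistic regression model will be used to evaluate the occurrence of severe adverse events as a secondary endpoint".

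The section Adverse event reporting and harms {22} sets the observation period for adverse events as "from the time of informed consent to day 28 of evaluation", and lists the start date among the items recorded for each event. The section on statistical methods {20a} applies intention-to-treat to all analyses. On missing data, section {21c} says "We will use multiple imputation for missing data".

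**The concern.** Patients enter over months and the look is set by an event count, so at the data cut-off some of them will have been followed for less than 28 days. The Cox model for efficacy takes each of them up to the cut-off and censors there. A logistic model on occurrence has no place for a follow-up time. A patient randomised the day before, with no event so far, must be scored as a no, be left out, or be imputed.

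Each of the first two options costs something. Scoring as a no gives a risk over an arbitrary mix of follow-up times, which lies below the day-28 risk that the collection window is built to measure. Leaving open-window patients out removes severe events that have already happened in them. Either way, the data monitoring committee has poorer absolute figures for harm than the data could give, at a look held partly for safety.

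**Working it through.** The documents give no severe-event rate or timing for this population. The sizes below rest on assumptions, marked as such.

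**1. The plan's own figure.** Inputs from Sample size {14}: hazard ratio 1.9, alpha 2.5% (two-sided), power 80%, 20% censoring, multiplier 1.5. Schoenfeld events for a 1:1 comparison: 4 × (2.241 + 0.842)² / (ln 1.9)² = 92.3. Then 92.3 / 0.8 = 115.4, rounded up to 116, and 116 × 1.5 = 174. The stated 174 is reproduced.

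**2. Timing of the look.** Read as primary-outcome events at the planned 80%, the total is 0.8 × 174 = 139 and half of that is 70.

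**3. Share of open windows, s.** Assumptions: uniform accrual, and exponential improvement times with 80% improved by day 28. In simulation, with the look at the 70th event:

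- 3-month accrual (from Study setting {9}: "The expected enrollment start date is April 21, 2020, and the expected end date is July 21, 2020"): about 107 enrolled, 51% under 28 days.
- 12-month accrual (Trial status: still recruiting in November 2020, end expected April 2021): about 93 enrolled, 15% under 28 days.

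A second simulation, with 70% control improvement and a hazard ratio of 1.0 or 1.9, gave 45–53% for 3 months, 25–30% for 6 months and 13–16% for 12 months.

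**4. If all randomised patients enter.** Let g be the average fraction of a patient's 28-day events already visible among open-window patients, whose follow-up is roughly uniform from 0 to 28 days. Then observed risk = true risk × [1 − s(1 − g)].

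- Events spread evenly over 28 days: g = 14/28 = 0.5.
- Early events (exponential, mean 5 days, truncated at 28): g = 1/(1 − e^(−5.6)) − 5/28 = 0.825.
- Late events (evenly over days 7 to 28): g = (21/2)/28 = 0.375.

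Assumed true risks are 20% (control) and 35% (drug): difference 15 points, odds ratio (0.35/0.65)/(0.20/0.80) = 2.15.

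| Accrual | Timing | Factor | Control | Drug | Difference | Odds ratio |
|---|---|---|---|---|---|---|
| 3 months | even | 1 − 0.51×0.5 = 0.745 | 14.9% | 26.1% | 11.2 | 2.01 |
| 12 months | even | 1 − 0.15×0.5 = 0.925 | 18.5% | 32.4% | 13.9 | 2.11 |
| 3 months | early | 1 − 0.51×0.175 = 0.911 | 18.2% | 31.9% | 13.7 | 2.10 |
| 12 months | early | 1 − 0.15×0.175 = 0.974 | 19.5% | 34.1% | 14.6 | 2.14 |
| 3 months | late | 1 − 0.51×0.625 = 0.681 | 13.6% | 23.8% | 10.2 | 1.98 |

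Direct simulation of the even case agrees: 14.7% versus 25.9% (11.2 points) with 3 months, and 18.3% versus 32.3% (14.0 points) with 12 months. With equal true risks in the arms, the odds ratio stays at about 1.0.

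**5. If only completed patients enter.** With 35% in both drug arms, the average true risk is (20 + 35 + 35)/3 = 30%. Even timing:

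- 3 months: events seen so far 107 × 0.30 × 0.745 = 24; events in completed patients 107 × 0.49 × 0.30 = 16. A third are discarded.
- 12 months: 93 × 0.30 × 0.925 = 26, against 93 × 0.85 × 0.30 = 24.

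Restriction gives unbiased day-28 risks but drops real events.

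**The case against.** A reader might infer that the plan counts recent patients as event-free. The article does not say so. It leaves the interim safety set undefined. Scoring every randomised patient is the natural reading under intention-to-treat, but restriction to closed windows would also fit the text. Multiple imputation is stated for missing data without saying whether that covers follow-up that has not yet happened. An analysis plan that is not shown may settle this.

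A reader might also infer that the committee will see understated harm set against a sound benefit estimate, so that the balance tilts towards the drugs. That goes too far. Concurrent blocked 1:1:1 allocation gives the arms similar follow-up, so the test is valid. The odds ratio, which is what a logistic model reports, falls only from 2.15 to 2.01 in the 3-month even case and to 2.11 in the 12-month case. The longer timeline is the more realistic one, given the Trial status section. The Discussion says of the drugs that "they require short-term use (only 4 days"); if harms cluster around dosing, the loss is smaller still. The committee is also unblinded and monitors adverse events directly.

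These points limit the size of the problem but do not remove it. The model is named in the protocol rather than left open, and section {20a} promises the analysis plan to the committee only before the final analysis, not before the interim. Restriction to completed patients is a workable alternative, but it pays with observed events.

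**Conclusion.** The point holds in a limited form. The interim harm model does not fit data with staggered entry: it either understates absolute risks and risk differences in every arm or discards severe events already seen. The validity of the comparison is not at stake, and the odds ratio moves little.

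Under the assumed 20% versus 35%, the 15-point difference shows as about 11 points with 3-month accrual and even timing, and about 14 with 12-month accrual. With early events it is about 13.7 to 14.6 points. These figures depend on assumed event rates, event timing, uniform accrual and improvement rate, none of which the documents fix for this purpose. The change is worth making because it is cheap and the look has a stated safety purpose, not because the present plan would mislead badly.

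**What to change.** In Interim analyses {21b}, replace the logistic model for severe adverse events by an analysis of time from randomisation to first severe adverse event, censored at the data cut-off. Report:

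- the cumulative incidence to day 28 per arm, with death without a prior severe adverse event treated as a competing event, unless death itself counts as one;
- a Cox hazard ratio for each drug against standard care.

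Logistic regression can stay for the final analysis, when all windows are closed.

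The cost is a short change of text and one extra time-to-event analysis. Event start dates are already collected and Cox is already planned for the same look, so no further patients or data are needed.
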